###### (iii) Ipsilateral Motor Pathways

This will be performed using a figure-of-eight-shaped coil (outer diameter of each loop 70 mm) connected to a Magstim stimulator (Magstim, Whitland, Dyfed, United Kingdom). The coil will be placed tangentially over the ipsilateral hand motor cortex with the handle pointing back and laterally 45° away from the midline at the optimal site for the activation of the APB. This is thought to be the best position for activating the pyramidal cells trans-synaptically and preferentially elicits late I-waves[62]. The direction of current induced in the brain will be anterior to posterior.

#### 4. Body functions and structures

The positive features of the UMN syndrome will be measured to grade the impact of intervention on the positive impairments and to compare severity between the groups after random allocation. Active and passive range of motion will be assessed primarily for the impaired shoulder, elbow, forearm (pronator teres), wrist flexors (flexor carpi ulnaris, flexor carpi radialis), fingers and thumb adductors (adductor pollicis) using goniometry[33]. Spasticity will be measured using the Modified Tardieu Scale[63] at fast velocity in the forearm agonists and the MAS[32,64] in the same muscle groups.

The negative features of the UMN syndrome will be measured to describe the sample and grade the effects of intervention. Each test will be performed in both the impaired (hemiplegic limb) and unimpaired (hand writing) UL to compare sensory function between limbs and evaluate the effects of treatment on both limbs. Two aspects of sensory impairment will be measured.

(i) Stereognosis will be assessed on the impaired and unimpaired limbs using the approach originally described by Feys[65]. Three familiar objects (teaspoon, key, peg) and six similar matched objects (safety pin and paperclip; pen and pencil; coin and button) will be used. With vision occluded, children will be presented with each item. A corresponding set of items will be used to allow children to identify the object in order to minimise any errors due to incorrect naming of the object.

(ii) Moving two point discrimination (M2PD) will be measured using the Disk-criminator® (Baltimore, Maryland) on both the impaired and unimpaired limbs. Either one or two points will be randomly applied in continuous moving firm contact longitudinally to the pulp of the index finger with vision occluded[66]. The minimum distance participants can usually distinguish between two discrete points, ranging from 2 mm (normal) to 15 mm (poor) were recorded[67].

(iii) Grip strength will be measured using a hand held dynamometer (Smedley, Takei Scientific Instruments Co Ltd). Grip strength will be measured for three attempts on the impaired and unimpaired limbs (kilograms force, Kgf) according to the guidelines of the American Society of Hand Therapists[68]. The mean of the three attempts will be used to compare limbs and to evaluate changes over time.

#### 5. Activity Outcomes

##### a) Unimanual capacity

###### (i) Melbourne Unilateral Upper Limb Assessment of Function (MUUL)

The MUUL[34] measures aspects of upper limb impairment and quality of upper limb function and will be the primary outcome measure. It consists of sixteen criterion-referenced items examining aspects of reach, grasp, release and manipulation. Each item has a set of scoring criteria with maximum possible raw score of 122. Raw scores are computed into percentage scores. The MUUL test has very high internal consistency (α = 0.96)[69]. Inter-rater and intra-rater reliability is very high for total test scores (ICC 0.95 and 0.97 respectively) and moderate to high for individual items (ICC 0.69 - 0.91). Test-retest reliability is moderate to high for items and high for total test scores[69]. The MUUL has established construct and content validity during test development[34]. Comparison of the MUUL and components of the Pediatric Evaluation of Disability Inventory (PEDI) yielded high correlation coefficients, further supporting construct validity[70]. Previous results of a reliability study found a change of 12% for intra-rater reliability and 14% for inter-rater reliability was required to suggest a clinically significant effect[34]. In a subsequent study investigating the interrater reliability and measurement error of the MUUL in a group of children with hemiplegia aged 5 to 8 years, results yielded a standard error of measurement (SEM) of 2.6% with the smallest detectable difference (SDD) of 8.9%[71]. A further investigation of interrater reliability and SEM of trained and untrained raters yielded SEM of 2.56 and 3.37 respectively[72]. Together these studies suggest that the SDD may be smaller than that originally published by Randall et al. However, reliability studies differ in terms of the study population in relation to age and type of CP, making it difficult to generalise results to our study population assessed by one trained rater masked to group allocation. Establishment of intra-rater reliability for this study is therefore required to determine the SDD and define children who achieve a significant clinical response.

###### (ii) Jebsen Taylor Test of Hand Function (JTTHF)

The JTTHF measures unilateral speed and dexterity on timed tasks[73]. The test measures speed and accuracy of performance on various complexities of grasp and release tasks using everyday items. The original test designed and validated in adults and typically developing children will be modified with omission of the writing activity and by reducing the maximum allowable time of each task to 2 minutes to both reduce frustration and allow comparison with similar studies in children with congenital hemiplegia[21,29,74]. The JTTHF has been shown to be responsive to change due to an intervention, however there are difficulties with stability of test-retest performance in the unimpaired limb[21,29,30,74].

##### (b) Bimanual performance

###### Assisting Hand Assessment (AHA)

Bimanual performance will be assessed using the AHA. This is a Rasch analysed measure of the effectiveness with which a child with a unilateral impairment makes use of his/her impaired hand in bimanual tasks[75]. The test consists of twenty-two items that are videotaped and each scored on a four point rating scale, yielding a range of scores between 22 and 88. Scaled scores are calculated by transforming the total raw score to a percentage and range from 25 to 100. Rasch analysis allows conversion of these ordinal scores into logits (log odds probability units) which are equal interval measures. Inter-rater reliability is high for summed scores (ICC 0.98) as is intra-rater reliability (ICC 0.99). There are three versions of the AHA; small kids, school kids and an adolescent version. Test-retest reliability is high for small kids (ICC 0.99) and school kids (ICC 0.98) and reliability between the two forms (small kids versus school kids) is also high (ICC 0.99). The AHA has been shown to be responsive to change due to an UL intervention[29,30]. Investigation of reliability yielded a SDD of 3.89 raw scores for the small kids and 3.65 raw scores for the school kids version[76]. The AHA requires standardised training and certification of raters[75]. The AHA will be scored by one certified rater whom will be masked to group allocation and order of assessment.

##### (c) Individualised outcomes

###### Canadian Occupational Performance Measure (COPM)

The COPM[77] is a standardised individualised, client centred measure that evaluates client's self perception of occupational performance over time. Client's identify areas of difficulty in everyday occupational performance and rate their performance and satisfaction for each problem on a scale from 1 to 10. An average score for performance and satisfaction is calculated. The COPM was designed for all ages and disability groups. There is good evidence of construct, content and criterion validity[78-80]. The retest reliability of the performance and satisfaction scores on the COPM is high (ICC 0.76-0.89)[81,82]. The COPM has demonstrated responsiveness to change in paediatric clinical trials[83,84]. A 2 point change on COPM performance has been reported as being clinically significant[77] In the present study the COPM will form the basis of goal setting for therapy. The COPM will be administered by one of the study occupational therapists with the child/adolescent and where necessary with parental input.

#### 6. Participation Outcomes

Three assessments were chosen to capture participation restrictions across home, school and community life based on a systematic review of participation measures for children with hemiplegia[85].

##### a) Assessment of Life Habits (LIFE-H for children version 1.0)

The LIFE-H is designed for children aged 5 to 13 years and measures life habits in home, school and neighbourhood environments[86,87]. It is a questionnaire completed by the parent/caregiver about the child. The child form is based on an adult version[86]. The long form consists of 197 items divided into 12 categories and includes regular activities (eating meals, communication, and mobility) and social roles. A weighted score ranging from 0 to 10 is generated for each category and overall total. Evidence of construct validity was established during test development[87] and criterion validity with strong correlations between the LIFE-H and PEDI and Functional Independence Measure for Children (WeeFIM)[88]. Adequate to excellent internal consistency (α 0.73 - 0.90 for categories, 0.97 for daily activities and 0.90 for social roles), intra-rater (ICC 0.83 - 0.95 for daily activities), inter-rater (ICC 0.8 - 0.91 for daily activities and 0.63 - 0.9 for social roles) and test-retest reliability (ICC 0.73 for total score) have been established[89]. Four categories will be evaluated in this study including nutrition (eg. mealtime activities), personal care (eg. dressing), education and recreation. These areas were considered to reflect many of the identified difficulties confronted by children with congenital hemiplegia that might be amenable to the intervention program.

##### (b) Children's Assessment of Participation and Enjoyment (CAPE)

The CAPE was designed to measure childrens participation in formal and informal leisure and recreation activities outside of school[90]. It evaluates five aspects of participation, including diversity (number of activities participated in), intensity (frequency of participation), with whom, where (the environment) and the level of enjoyment. Scores can be generated for formal and informal domains and five activity types. Total test diversity scores can range from 0 to 55 and intensity scores from 1 to 7. These are the two areas of interest in this study. Content and construct validity were established during test development[90] and in a subsequent validation study[91]. Test-retest reliability is adequate for diversity (ICC 0.67-0.77) and intensity (0.72-0.81) and high for inter-rater reliability (0.82-0.99)[90]. The interview method of administration will be used, with the expectation of establishing rapport with the children in the study.

##### (c) School Function Assessment (SFA)

The SFA evaluates a child's performance in a range of functional tasks that are necessary for participation in academic and social activities in primary school[92]. The first section of the assessment specifically measures participation in six school activity settings (general or special education classroom, playground, transportation to and from school, bathroom, transitions to and from the classroom and mealtimes). The remaining two sections measure activity performance and task supports. All three sections can be administered independent of each other,[92] so in order to reduce burden, only the participation domain will be used. The SFA has established validity using expert panels and factor analysis[92,93]. The SFA has high internal consistency (Cronbachs alpha (α) 0.92 - 0.98 for scales), excellent test-retest reliability (ICC 0.80 - 0.99) and adequate interrater reliability (ICC 0.70 for participation)[92,94]. The participation section will be completed by the child's teacher during a telephone interview.

#### 7. Environmental Measures

##### (a) The Craig Hospital Environmental Factors (CHIEF)

This is a generic measure that evaluates the impact of attitude and support barriers, services and assistance barriers, physical and structural barriers, policy barrier, and work and school barriers to participation. It has excellent established reliability with high test-retest (ICC 0.93 for total score) and internal consistency (α = 0.93) and good content and discriminant validity[95].

##### (b) The Study Questionnaire

A study questionnaire was developed to capture demographic information that has been shown in the literature to influence a child's participation. These include family ethnicity, socio-economic status, family structure and supports, and family interests. A measure of social advantage/disadvantage will be derived from postcode of residence using the Index of Relative Socio-economic Advantage/disadvantage (2006) from the Australian Bureau of Statistics[96]. Deciles will be reported on a continuum with lower scores reflecting greater socio-economic disadvantage and higher scores reflecting socio-economic advantage.

#### 8. Quality of Life

##### (a) The Cerebral Palsy Quality of Life Questionnaire for Children (CPQOL-Child)

The CPQOL-Child[97] will be used to capture parental report of their child's perceptions of quality of life (CPQOL Primary Caregiver Questionnaire). For children and youth of nine years or older, the CPQOL Child Report Questionnaire will also be used to measure children's own perceptions of their quality of life. Results of factor analysis demonstrated that the CPQOL-Child measures 7 broad domains of quality of life: social wellbeing and acceptance, functioning, participation and physical health, emotional wellbeing, access to services, pain and impact of disability and family health. The internal consistency ranges from 0.74-0.92 and 2 week test re-test reliability ranges from 0.76-0.89. As expected, the domains moderately correlated with the CHQ, KIDSCREEN, and GMFCS. The CPQOL-Child is designed to be used to evaluate the effectivness of interventions for children with cerebral palsy and to gain further understanding about the determinants of QOL. The CPQOL-teen version for youth 14-18 years was not available at the commencement of the present study so that the child version was used for the entire sample. A recent publication has confirmed that the domains for the Teen version are very similair to the Child version[98].

##### (b) Kidscreen

In addition to the condition specific QOL tool, the CPQOL-child, a generic measure will be used to compare parents report of QOL for children with CP compared to their age, gender and environmentally matched peers (the buddies). The Kidscreen has been described as the most useful generic measure of QOL of children as it addressed the multidimensional construct of QOL through various domains and focused specifically on the well-being of children, as the defined by the WHO definition of QOL[99]. It was developed to implement the views of children, through focus group work of 3000 children[100]. The questionnaire takes only 15-20 minutes to complete. The KIDSCREEN-52 Questionnaire consists of 52 questions across 10 domains. These domains include 1) Physical Well-being, 2) Psychological Well-being, 3) Moods and Emotions, 4) Self-Perception, 5) Autonomy, 6) Parent Relations and Home Life, 7) Social Support and Peers, 8) School Environment, 9) Social Acceptance (Bullying), 10) Financial Resources. A child self report was administered for children 8-18 years old and a parent proxy version was administered for parents of children 5-18 years. Children below the age of 8 were unable to self-report as their reports were likely to be unreliable. Reliability was calculated by Chronbach's Alphas and ranged between 0.76 and 0.89 throughout the 10 domains of HRQOL. Convergent and discriminant validity were tested using information of child's physical and mental health. Correlations of up to 0.55 were found when correlating the KIDSCREEN-52 dimensions with frequency of physical complaints[100].

### Comparison to Typically developing children

Fifty-two typically developing peers ("buddies") matched with the study participants according to age, gender and classroom that they attend will be invited to participate. Typically developing children in this 'bring a buddy" system will be assessed at baseline, 26 and 52 weeks to provide a reference for participation in home, school and community life and QOL. At study entry the typically developing age and gender matched controls "the Buddies" will meet the following criteria:

### Inclusion Criteria

1. Typical development with no history of upper limb dysfunction, developmental or learning disability.

### Exclusion Criteria

1. Diagnosis of learning disability, developmental disability, history of behavioural problems, visual or hearing difficulties that would impact on function and participation.

2. History of congenital or acquired upper limb dysfunction.

The procedure for recruiting the "buddies" is that they will be identified by the study participants and their families, and will be in the same class at school and be invited to participate by the child with hemiplegia in the study. Once "buddy" participants agree to be contacted by the researchers they will be sent an information statement and consent form, followed by telephone contact to arrange time for an initial assessment. At the initial assessment the study and assessment procedure will be explained and the "buddy" will be screened. Each buddy will be assessed on the CAPE, LIFE-H, and Kidscreen to provide comparison data for the study sample. Only children attending regular school will be invited to participate to provide an age, gender and environmentally matched reference sample.

### Analyses

All assessment forms will be developed using scannable Teleforms (Teleform, 2005). Forms will be entered, scanned and visually checked by staff trained in use of the software. Data will be transferred electronically into Microsoft Access 1997. Analyses will be on an intention-to-treat basis using STATA 10. Data from each outcome measure will be summarised for each treatment group and descriptive statistics (frequencies, means, medians, 95% confidence intervals) calculated dependent on data distribution. We anticipate that groups will be similar on baseline measures due to the matched pairs design. Initially between group differences will be evaluated at the three follow-up assessment points using independent t-tests or Wilcoxon rank sum test. Within group changes between baseline and the follow-up assessments for continuous variables will be evaluated using paired t-tests or Wilcoxon matched-pairs sign rank test. A significance level of 0.05 will be used.

For the TMS data Student's paired t-test will be used for analysis of the difference between pre and each post intervention (3 and 26 weeks) mean MT and MEP ratios. This will be performed in each group for the impaired side and the unimpaired side.

To determine the intra-rater reliability of our trained occupational therapist rater on the MUUL, intraclass correlation coefficients will be calculated (3.1) with 95% confidence intervals from total MUUL percentage scores[101]. The standard error of measurement (SEM = SD × √(1-ICC)) and the smallest detectible difference (SDD = SEM × 1.96 × √2) will be calculated[102].

Post hoc analyses will be undertaken to investigate clinical characteristics of children who have a greater response to either intervention.

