### Sample size

According to CONSORT guidelines the primary basis for sample size calculation is adequate power for the comparison between the functional effects of CIMT and BIM training at 3 weeks post intervention. Based on data from a previous study[33], a mean difference of 7 percentage points was proposed or 10% of the anticipated control group mean at baseline on the Melbourne Assessment of Unilateral Upper Limb Function[34] as the minimum difference that is likely to have substantial clinical importance. Our pilot data in a study of UL training with and without intramuscular BoNT-A injections yielded standard deviation of changes of 7.6 and 9.6 units in the two groups. Based on a t-test comparison of changes using a SD of 9 units for both groups, significance (alpha) level of 0.05, and 80% power, we require 26 participants in each group (total sample of 52).

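### The 80% power is for a comparison of changes from baseline, but the between-group test described in the Analyses section names no baseline term

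*Protocol article*

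**What the plan says.** The Sample size section fixes the analysis that the trial is powered for: "Based on a t-test comparison of changes using a SD of 9 units for both groups". The SD of 9 is a change-score SD. It is taken from pilot work that "yielded standard deviation of changes of 7.6 and 9.6 units in the two groups". The target is stated as "a mean difference of 7 percentage points was proposed", with "significance (alpha) level of 0.05, and 80% power", and the result is 26 children per group.

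The Analyses section first remarks: "We anticipate that groups will be similar on baseline measures due to the matched pairs design". The next sentence gives the treatment comparison: "Initially between group differences will be evaluated at the three follow-up assessment points using independent t-tests or Wilcoxon rank sum test". The sentence after that uses change from baseline, but for within-group paired tests. The section names no between-group test of change, no baseline covariate and no pair term.

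The Randomisation section matches pairs on age band, gender, side of hemiplegia and screening MUUL, and baseline assessments are completed before randomisation.

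**The concern.** An independent t-test on follow-up scores has the between-child SD of the score in its error term. A t-test on changes has the SD of change. These are different quantities, and they coincide only at a baseline/follow-up correlation of 0.5 (with equal SDs). Where children keep their rank from one assessment to the next, the score SD is the larger of the two.

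If the follow-up-score test is the one carried out, the trial could miss a 7-point difference that it is described as having 80% power to detect. A null result on the primary outcome would then be hard to interpret. Baseline MUUL is available for every child, so the loss would be avoidable.

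**Working it through.** **Inputs from the Sample size section.** Difference 7 points; SD of change 9 in both groups; alpha 0.05; power 80%; 26 per group. Sidedness is not stated, but two-sided reproduces the figure (one-sided would give 21 per group).

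**Step 1: reproduce the plan's figure.** n per group = 2 × (1.96 + 0.8416)² × (9/7)² = 25.95, so 26. Exact power with the noncentral t at 26 per group is 78.5% (80.1% by the normal approximation). The sample size is therefore right for a comparison of changes.

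**Step 2: link the change SD to the score SD.** Assume equal SDs at baseline and follow-up, with correlation rho. Then SD of change = SD of score × √(2(1 − rho)), so SD of score = 9 / √(2(1 − rho)). The article gives neither rho nor the score SD, so rho is an assumption and is shown as a range.

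**Step 3: power for 7 points at 26 per group, two-sided 0.05, exact t.** The ANCOVA residual SD is SD of score × √(1 − rho²).

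| rho (assumed) | SD of score | Unadjusted test of follow-up scores | ANCOVA residual SD | ANCOVA, no pair term | ANCOVA, fixed pair terms |
|---|---|---|---|---|---|
| 0.5 | 9.0 | 78.5% | 7.8 | 89% | 87% |
| 0.6 | 10.1 | 69% | 8.0 | 87% | 85% |
| 0.7 | 11.6 | 57% | 8.3 | 85% | 83% |
| 0.8 | 14.2 | 41% | 8.5 | 83% | 81% |
| 0.9 | 20.1 | 23% | 8.8 | 81% | 79% |

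The last column charges the 25 degrees of freedom that 26 pairs use up and credits no further reduction in variance, so it is a cautious figure.

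**Step 4: rough plausibility check on the score SD.** The MUUL section quotes a standard error of measurement of 2.6 and reliability coefficients of 0.95 and 0.97. SD = 2.6/√(1 − 0.95) = 11.6 and 2.6/√(1 − 0.97) = 15.0, which correspond to power of about 57% and 38%. These inputs come from different reliability studies, and the section itself warns that such results may not carry over to this sample. The check shows that a loss is plausible. It does not establish its size.

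**Step 5: does matching rescue the unpaired test?** It does not, because an independent t-test ignores the pairing. In simulation with within-pair correlation from 0.3 to 0.7, its power was 55% to 57% at a score SD of 12, and 41% down to 37% at a score SD of 14.

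**The case against.** The strongest reply is that the Analyses section does not say which quantity is tested at each follow-up point. An independent t-test on changes at each point would satisfy both sections, and the Sample size section is explicit about changes. That reading is possible but less natural: the very next sentence speaks of changes when changes are meant, and there they are within-group. If change was intended, the wording still needs to say so.

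A second reply is that the word introducing these tests marks a first step, so adjusted models may follow in a fuller document. The article describes no later adjusted between-group comparison. It goes on to within-group tests, the TMS tests, rater reliability and post hoc responder analyses. The point rests on the test that is named, not on detail left out.

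Three stronger inferences are tempting and are not supported:

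- A reader might infer that baseline is left out because matching is expected to balance the groups. The two sentences are adjacent, but the text does not state that reason.
- A reader might infer that power is roughly halved. That needs a correlation of about 0.8; at 0.5 nothing is lost, and the article does not give the correlation.
- A reader might infer that a chance baseline gap would pass freely into the treatment estimate. For MUUL, matching on the screening score limits that gap.

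**Conclusion.** The powered test and the stated test differ on the natural reading of the Analyses section. The 26 per group is correct for changes with SD 9. For unadjusted follow-up scores, the 80% holds only if the baseline/follow-up correlation is about 0.5 or lower. Over correlations of 0.5 to 0.9, power runs from 78.5% down to 23%, assuming equal SDs and a change SD of 9. The mismatch is in the text; the size of the loss is conditional on a correlation that the article does not report. Similar group means at baseline do not alter this, because matching does not shrink the error SD of an unpaired, unadjusted t-test.

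**What to change.** In the Analyses section, make the between-group comparison of MUUL an ANCOVA of the follow-up score on treatment with baseline MUUL as covariate, preferably also accounting for pair. Use the same form for other outcomes that have a baseline value. In the Sample size section, state that the power refers to this analysis. At correlations of 0.7 to 0.9 the present 52 children give about 85% to 81% power without a pair term. With fixed pair terms and no variance gain, the figures are about 83% to 79%.

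At minimum, state that the between-group tests are on change from baseline, as powered.

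Also reconcile the time point to which the primary analysis applies: the Sample size section refers to 3 weeks after intervention, whereas the Primary and Secondary Outcome Measures section refers to 26 weeks.

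The cost is wording only. Baseline values are already collected, and the sample size need not change.

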**Methods/Design:**

A matched pairs randomised comparison design will be used with children matched by age, gender, side of hemiplegia and level of upper limb function. Based on power calculations a sample size of 52 children (26 matched pairs) will be recruited. Children will be randomised within pairs to receive either CIMT or BIM training. Both interventions will use an intensive activity based day camp model, with groups receiving the same dosage of intervention delivered in the same environment (total 60 hours over 10 days). A novel circus theme will be used to enhance motivation. Groups will be compared at baseline, then at 3, 26 and 52 weeks following intervention. Severity of congenital hemiplegia will be classified according to brain structure (MRI and white matter fibre tracking), cortical excitability using Transcranial Magnetic Stimulation (TMS), functional use of the hand in everyday tasks (Manual Ability Classification System) and Gross Motor Function Classification System (GMFCS). Outcomes will address neurovascular changes (functional MRI, functional connectivity), and brain (re)organisation (TMS), body structure and function (range of motion, spasticity, strength and sensation), activity limitations (upper limb unimanual capacity and bimanual motor coordination), participation restrictions (in home, school and recreation), environmental (barriers and facilitators to participation) and quality of life.

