### Randomisation

Children will be matched in pairs according to age (12 month age bands), gender, side of hemiplegia, and level of functional ability based on MUUL scores at screening. Once matching has been achieved and baseline assessments completed, children will be randomised within pairs from concealed envelopes opened by non-study personnel. Treatment allocation will be recorded on a piece of folded paper inside each envelope in random order (computer generated). The randomisation process will involve allocating a number "1" or "2' to each member of the pair which will be written on the paper inside the envelope. As each pair is entered, they will be allocated the next consecutive envelope, which will be opened by the non-study personnel who will read and record the treatment allocation from the paper inside the envelope. Study personnel will be informed of group allocation.

A matched pairs design is the design of choice as it minimises the likelihood of group differences at baseline that has often been present in UL rehabilitation studies[21,29]. In order to maximise group coherence, camps will be conducted in two age bands (two camps each of CIMT and BIM training for children 5-10 years and one camp each of CIMT and BIM training for children 11-16 years).

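### Children are randomised within matched pairs, but the between-group tests ignore the pairs; the comparison is conservative, with a loss that runs from negligible to large depending on which score is tested

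*Protocol article*

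**What the plan says.** The design is paired. The abstract plans 26 pairs: "Based on power calculations a sample size of 52 children (26 matched pairs) will be recruited". The Randomisation section gives the matching factors, with the MUUL level taken before entry: "Children will be matched in pairs according to age (12 month age bands), gender, side of hemiplegia, and level of functional ability based on MUUL". It then says that "children will be randomised within pairs from concealed envelopes opened by non-study personnel". The reason it gives for matching is baseline balance: "A matched pairs design is the design of choice as it minimises the likelihood of group differences at baseline".

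The between-group analysis is unpaired. The Analyses section says: "Initially between group differences will be evaluated at the three follow-up assessment points using independent t-tests or Wilcoxon rank sum test". Paired tests do appear in that section, but for a different comparison: "Within group changes between baseline and the follow-up assessments for continuous variables will be evaluated using paired t-tests or Wilcoxon matched-pairs sign rank test". The transcranial magnetic stimulation data also get a paired t-test, again before against after within each group. No between-group analysis that uses the pair is named. The opening word of the between-group sentence suggests a first step, but the only further treatment-related analysis in the section is a post hoc look at characteristics of responders.

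The Sample size section is unpaired as well: "Based on a t-test comparison of changes using a SD of 9 units for both groups, significance (alpha) level of 0.05, and 80% power", giving 26 per group.

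**The concern.** Randomising within pairs makes the pair a block, and the analysis should reflect it. Partners are matched on screening MUUL, and MUUL is the primary outcome, so some positive correlation between partners at follow-up is to be expected. An independent-samples test leaves that covariance out of the standard error. The reported interval is then wider, and the p-value larger, than the design warrants.

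With 52 children, the practical risk is missing a real difference between two active treatments. A non-significant result could then be read as showing that the two approaches do equally well.

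**Working it through.** **1. Reproduce the planned sample size.** Inputs from the Sample size section: difference 7, SD of change 9, alpha 0.05 (sidedness not stated; two-sided reproduces the figure), power 80%.

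n per group = 2 × [9 × (1.960 + 0.842) / 7]² = 25.95, rounded up to 26.

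This matches the plan. By the exact t distribution, power at 26 per group is 78.5%. The calculation takes no credit for pairing.

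**2. Effect of ignoring the pairs.** Let r be the within-pair correlation in whichever score is analysed. The documents give no r, so a range is assumed.

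- Standard error used by the unpaired test: 9 × sqrt(2/26) = 2.50.
- True standard error: 9 × sqrt(2(1−r)/26).
- Ratio: 1/sqrt(1−r).

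Paired power is by the noncentral t with 25 degrees of freedom. Unpaired type I error and power are simulated, 100,000 trials per value of r.

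| r (assumed) | True SE | Unpaired SE too large by | Type I error, unpaired (nominal 5%) | Power, unpaired | Power, paired |
|---|---|---|---|---|---|
| 0 | 2.50 | 0% | 5.1% | 79% | 77% |
| 0.1 | 2.37 | 5% | 4.1% | 80% | 81% |
| 0.2 | 2.23 | 12% | 2.9% | 81% | 85% |
| 0.3 | 2.09 | 20% | 2.0% | 83% | 90% |
| 0.5 | 1.77 | 41% | 0.7% | 86% | 97% |

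The 5.1% at r = 0 is simulation noise around 5%. Break-even in power is near r = 0.05. Below that, the paired test is slightly worse because it has 25 rather than 50 degrees of freedom.

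**3. Which r is plausible depends on the score analysed.** Take a simple model in which partners resemble each other only through matched baseline level. Assume a baseline-to-follow-up correlation of 0.8 and a within-pair correlation at baseline of 0.7.

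- Score variance implied by a change SD of 9: 81 / [2(1−0.8)] = 202.5, so SD = 14.23.
- Within-pair correlation of follow-up scores: 0.8² × 0.7 = 0.448.
- Within-pair correlation of change scores: (1−0.8)² × 0.7 × 202.5 / 81 = 0.07.

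*Change scores.* Power is about 79% unpaired and between 79% and 80% paired. Type I error of the unpaired test is about 4%. Pairing gains almost nothing here.

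*Raw follow-up scores, no baseline.* The unpaired test uses a standard error of 14.23 × sqrt(2/26) = 3.95. The true value is 3.95 × sqrt(1−0.448) = 2.93. Simulated power is about 39% unpaired against 63% paired. Null rejection is about 1% against 5%.

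**4. Separate the two causes in the raw-score case.** With SD 14.23 and no pairing at all, an independent t-test on 26 per arm has about 41% power (noncentrality 7/3.95 = 1.77, 50 degrees of freedom). The drop from 79% to about 40% therefore comes from discarding baseline. Analysing the pairs recovers part of it, up to 63%, because a matched partner carries some of the baseline information.

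**The case against.** The strongest reply is that nothing planned is lost. A reader might infer that matching was chosen for power and that the analysis throws this power away. The documents do not support that. The Randomisation section cites only baseline balance, and the sample size rests on an unpaired test of changes. If changes are compared, the planned power of about 80% stands, and only extra efficiency that nobody claimed is forgone. This part of the objection stands.

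It is also fair that the low raw-score power mixes two matters, pairing and baseline adjustment, and that the Analyses sentence does not say outright whether scores or changes are compared. The 39% should therefore not be read as the trial's power. It holds only if raw follow-up scores are tested and the two assumed correlations are about right.

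Third, the article condenses a fuller plan, and its between-group sentence presents the tests as a first step. This helps little: the article names specific tests, those tests do not fit its own randomisation, and no later between-group model is mentioned.

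Finally, a paired t-test or signed-rank test drops both children when one is lost, which sits badly with intention-to-treat analysis over 52 weeks. This is right, and it argues for a mixed model over a simple paired test.

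**Conclusion.** The mismatch is real: randomisation is within matched pairs, and the only between-group tests named ignore the pairs. For positive r, the standard error is overstated by 1/sqrt(1−r) and the test is conservative.

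A reader might go further and infer biased results or spurious positives; neither follows. With complete pairs, the mean difference is the same under both tests, and for r of zero or above the unpaired type I error does not exceed the nominal level beyond simulation noise.

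The size rests on an r that the document does not give. For change scores, the loss is nil to about 4 points of power for r up to 0.2. For raw follow-up scores without baseline, it is about 24 points (39% against 63%) under the assumed correlations of 0.8 and 0.7. This is a cheap improvement that should be made, not a flaw that threatens the trial.

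**What to change.** In the Analyses section, replace the independent t-test or rank-sum test for the between-group comparison with a linear model of follow-up MUUL on treatment and baseline MUUL, with pair as a random effect. This respects the randomisation, settles whether baseline is used, and keeps a child whose partner is lost. Use the same form for the continuous secondary outcomes, each with its own baseline value. Keep the paired t-test or signed-rank test on within-pair differences as a sensitivity analysis only, because it drops incomplete pairs.

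The change is to wording; sample size and data collection are unaffected. If matching proves uninformative, the cost is up to about 2 points of power (77% against 79% at r = 0 for the simple paired test).
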